**Discussion:**

The purpose of this two-phase trial is to compare the clinical effectiveness of focused vision-guided meditation with Chinese eye exercises that are also non-pharmacological, non-invasive interventions for myopia, and to maximize the benefit to the subjects. The results will indicate whether the training based on focused vision-guided meditation has the ability to improve distant visual acuity, relieve ocular symptoms, and ameliorate diopter. In addition, this trial will provide clinical efficacy of the training, which is expected to provide meaningful data for vision rehabilitation. At the same time, the vision acuity training method, which is permeated with the concept of Traditional Chinese Medicine (TCM) rehabilitation and health maintenance, will be applied to achieve the goal of preventing or alleviating myopic development and reducing myopia rate.

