**Fig. 1 Fig1:**
[figure not shown]
Study design

**Table 1 Tab1:** General procedure and monitoring process

		Study period														
		Enrollment	Allocation	Intervention (phase 1)				Follow-up			Intervention (phase 2)				Termination	Unscheduled visit
Time point		–7~0 d^*****^	0 d	1st d^*****^	2~7d	8th d^*****^	9~30d	M1^*^	M2	M3	1st d	2~7d	8th d	9~30d		

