### Intervention description

The vision acuity training of this study is conducted in the schools, and school leaders are fully aware of this project, support, and cooperate with the research work. Relevant teachers will be designated by the schools to be responsible for this project with respect to the specific matters concerned. The study will be conducted in two phases over a period of 8 months, with a training period of 30 days in each phase and a follow-up of 3 months. No interventions will be conducted during the treatment period and follow-up period. One visual acuity examination will be performed in each of the two phases at months 1, 2, and 3 of the follow-up.

### Phase 1

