#### Second phase

After the completion of the first phase of the randomized controlled study, data will be collected and compared between the vision acuity training group and the Chinese eye exercise group.

The second phase will be carried out based on the experimental results of the first phase. If the first phase showed that the visual training effect was not significantly better than eye exercises, the trial was terminated. If the data proved that the effect of the meditation group was not superior to the control group, and the results were statistically significant, the second phase of the experiment will be carried out.

Since the purpose of this study is to improve the naked eye visual acuity that affects life and work, the experimental group has achieved this effect in the first stage. In order to ensure the maximum benefit of the subjects, only the control group and the experimental group of the first stage were given the same treatment plan in the second stage, namely guided meditation for vision acuity training. The results of phase 2 subjects (the control group at phase 1) were compared with the results of eye exercises at phase 1.

The subjects in this study are adolescent students with simple myopia and no other comorbidities of chronic diseases. If the subjects need to combine medication due to cold or other reasons, they should be recorded promptly.

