Meditation is vital for “mental condition adjustment” and “health improvement” in TCM and has been advocated and practiced by medical practitioners in ancient China. It is also one of the populated approaches for self-health management. Meditation is often coordinated with the adjustment of posture, breathing, and consciousness to motivate self-healing capacity. It means to build a peaceful and perceptive mind to overcome the judgmental thoughts or emotions. This helps to eliminate unhealthy muscle memories and psychological preconceptions, potentially creating new ways to cope with illness [26]. Studies have shown that during meditation, parasympathetic activity increases and sensory and perceptual changes occur. These physiological changes are a state of self-healing relaxation that may have preventive and therapeutic effects on human health [27]. Meditation is also a positive mental exercise that alters brain and mind function and facilitates the regulation of attention, cognition, and mood. It is well documented that mental state affects physical condition, and its imbalance affects hormone release, attributing to diseases.

The incorporation of meditation elements into vision acuity training is a multifaceted combination of movement, breathing, and imagination, which may enhance vision by strengthening the eye muscle regulation functions.

This project will be conducted in two phases, using two research designs. The first phase will be a multicenter randomized controlled study, and the second phase will be a single-arm pre-post controlled study. The aim is to compare the differences in the effects of the training based on guided meditation and Chinese eye exercises on vision regulation in adolescents. If the significant clinical efficacy and safety are uncovered, a novel non-pharmacological physical therapy will be provided for the treatment of adolescent myopia. The study will also help to promote and disseminate the vision acuity training method, which is infused with the TCM rehabilitation concept, and provide a reference plan and basis for solving the myopia problem among adolescents.

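### Phase 2 sets the control children's meditation results against their own earlier eye-exercise results, in fixed order with no concurrent comparator, so it cannot support an efficacy conclusion; Table 1 also omits the phase 2 follow-up.

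*Protocol article*

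**What the plan says.** The Second phase section moves the phase 1 control children to guided meditation and then prescribes the comparison: "The results of phase 2 subjects (the control group at phase 1) were compared with the results of eye exercises at phase 1". On who is treated, the same section says that "only the control group and the experimental group of the first stage were given the same treatment plan in the second stage". Table 1 lists only a control-group row for phase 2.

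The main Discussion names the design: "the second phase will be a single-arm pre-post controlled study". Right after describing both phases, it gives a comparative purpose: "The aim is to compare the differences in the effects of the training based on guided meditation and Chinese eye exercises". The abstract does the same for the trial as a whole: "The purpose of this two-phase trial is to compare the clinical effectiveness of focused vision-guided meditation with Chinese eye exercises".

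On timing, Intervention description says: "The study will be conducted in two phases over a period of 8 months, with a training period of 30 days in each phase". It then adds: "One visual acuity examination will be performed in each of the two phases at months 1, 2, and 3 of the follow-up". In Table 1 the only block of months 1 to 3 stands before the columns headed "Intervention (phase 2)". After phase 2 days 9 to 30 the table goes straight to Termination.

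**The concern.** A before-and-after comparison in a fixed order has no way to separate the second treatment from whatever else differs between the two periods. Here that includes growth and myopia progression in children aged 8 to 18, any lasting effect of the eye exercises, familiarity with the chart, and the point in the school year. Children and those delivering the training also know what is being given (Implementation).

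At stake is how a phase 2 difference would be read. The plan prescribes a comparison with eye exercises and gives the two-phase trial a comparative purpose, and nothing in the article limits phase 2 to description. A significant result could therefore be reported as a second demonstration that meditation beats eye exercises.

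The schedule raises a separate, practical problem. A site that works from Table 1 would not examine children at months 1 to 3 after phase 2, although the text requires it.

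**Working it through.** **1. Structure of the comparison.** Every child in it follows one path: eye exercises for 30 days, follow-up for 3 months, meditation for 30 days. Start to start, the gap is 1 + 3 = about 4 months. The wording on whether the phase 1 experimental group is treated again is unclear, but on either reading nobody receives eye exercises in phase 2. Treatment and period therefore coincide completely.

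**2. Chart practice.** Primary observation indexes schedules a test before and after each session for 7 days (14), then weekly to day 30 (about 3), then 3 follow-up tests. That is 14 + 3 + 3 = about 20 acuity tests before phase 2 begins.

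**3. Conditional start.** Phase 2 depends on the phase 1 result. The sentences setting that condition contradict each other and need reconciling. If phase 2 opens only after a significant result for meditation, the phase 1 control results will tend to be low by selection. Those same results are the phase 2 comparator, so this element would favour phase 2.

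**4. Duration.** The stated 8 months is reproduced by two phases, each with 1 month of training and 3 of follow-up: 1 + 3 + 1 + 3 = 8. Table 1 as printed gives 1 + 3 + 1 = 5, if Termination follows directly on phase 2 training. Termination carries no time label, so the 5 is an inference. That no month 1 to 3 columns follow phase 2 is plain from the table.

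**5. Size of a misleading shift (illustration).** The article gives no sample size or power for phase 2, so there is no plan figure to reproduce.

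- From Sample size: 380 controls less 20% dropout, 380 × 0.8 = 304; control SD 0.24; two-sided 0.05; planning difference 4.98 − 4.92 = 0.06.
- Assumed: within-child correlation r of 0.5 to 0.8, equal between all time points; a non-treatment shift of 0.03 (half the planning difference); no true difference between treatments.

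The article does not say whether levels or changes are compared, so both are shown. The chance of significance is Φ(0.03/SE − 1.96); the opposite tail is negligible.

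*Levels:* SE = 0.24 × √(2(1 − r)) / √304.

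*Each phase's own change:* two changes are differenced, so SE = 0.24 × √(4(1 − r)) / √304.

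| Comparison | r | SE | 1.96 × SE | Chance of p < 0.05 with shift 0.03 |
|---|---|---|---|---|
| Levels | 0.5 | 0.0138 | 0.027 | 59% |
| Levels | 0.8 | 0.0087 | 0.017 | 93% |
| Changes | 0.5 | 0.0195 | 0.038 | 34% |
| Changes | 0.8 | 0.0123 | 0.024 | 68% |

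With no shift, each of these would be 5%. The lower two rows apply only to the part of a shift that does not cancel. A steady drift enters both 30-day changes equally and drops out; uneven period effects, carry-over and learning do not.

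**The case against.** The best defence is that the limitation is disclosed. The Discussion says openly that phase 2 is single-arm and pre-post. The stated reason for it is benefit to the subjects, which in practice gives the control children later access to the training. No hypothesis, sample size or power is attached to it. This stands as far as it goes: a reader might infer that the protocol presents phase 2 as confirmatory, and no section says so. But naming the design does not limit the conclusion drawn from it, and the article both prescribes the comparison with eye exercises and states a comparative purpose for the two phases together.

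A second objection is that a pre-post analysis would use phase 2's own baseline. Table 1 does schedule acuity at month 3 and on phase 2 day 1, so this is possible and would remove steady drift. It is why the 59 to 93% range cannot stand alone as the size of the problem. It does not remove carry-over, practice or the conditional start.

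A reader might also infer that children are told the phase 1 result before phase 2. The article says only that subjects know their assignment and that phase 2 depends on phase 1; it reports no announcement. Nor can one assume that the bias must favour meditation: progression would lower acuity, practice would raise it, and the net direction is unknown.

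Finally, the gap in Table 1 is a scheduling contradiction. It is not the reason the comparison fails; the design point holds without it.

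**Conclusion.** The point holds, limited to what phase 2 can show. The planned comparison is fully confounded with period, carry-over, chart practice and the conditional start, and it cannot support an efficacy conclusion against eye exercises. This follows from the design alone and needs no assumption. It would be wrong to extend it to phase 1, whose randomised comparison is untouched.

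The size is illustrative. A 0.03 shift unrelated to treatment would be declared significant about 59 to 93% of the time on levels, or about 34 to 68% on changes where the shift does not cancel. The size of the shift and the correlation are assumptions.

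Separately, the text and Table 1 contradict each other on phase 2 follow-up: 8 months with examinations at months 1 to 3 in each phase, against a table with no such columns after phase 2. If Table 1 is followed, those readings are lost, and months 1 to 3 after meditation cannot even be described.

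**What to change.** - State that efficacy conclusions against eye exercises rest on the randomised phase 1 comparison only.
- Report phase 2 descriptively, as within-child change from phase 2's own baseline with a 95% CI, in place of the comparison with phase 1 eye-exercise results.
- Reconcile Table 1 with Intervention description on the phase 2 examinations at months 1 to 3.

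It may be tempting to rescue the comparison by estimating drift from the control children's months 1 to 3 after phase 1. This is not recommended: those months mix drift with the fading of any eye-exercise effect, and three monthly readings cannot separate them.

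The cost is wording and a corrected schedule. If reconciliation keeps the examinations that the text already promises, Table 1 has to schedule them. The downside is that phase 2 can no longer be presented as a second comparison with eye exercises.

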### Basic information collection

Information will be collected from the subjects before the start and after the trial is completed, and the main information is as follows.
Basic information: age, nation, grade, height, weight, family history of myopia, parents’ high myopia, etc.Myopia: duration of myopia, possible causes of myopia, naked eye visual acuity, corrected visual acuity, diopter of both eyes, astigmatism, and so onTime allocation for daily activities: including close-range activities (< 50 cm): such as drawing, homework, reading, and using electronic screen terminals such as mobile phones; outdoor activities: including playing outdoors, cycling, hiking, etc.

### Primary observation indexes

Visual acuity training aims to improve naked eye visual acuity, which affects life and work and will be used as the main observation index. Visual acuity tests were performed before and after each training session for the first 7 days, once a week after 7 days of training and at the first, second, and third months of follow-up, respectively.

The specification for visual acuity testing is based on the “Expert Consensus on Workflow of Myopia Screening in Children and Adolescents (2019)” [21]. The international standard logarithmic visual acuity chart is adopted. During the measurement, the subjects stand 5 m away from the visual acuity chart and cover the contralateral eyes without squinting and oppression. The covered eyes are examined first in the right eye and then in the left eye. If the inspector can identify half or more of the visual markers, check them line by line from top to bottom and ask the subjects to say or gesture the direction of the gap of the visual markers within 5 s. The last line of the visual markers that is correct will be the testee’s vision of that eye. For example, if row 4.8 cannot be identified, check upward until half or more of the rows can be identified.

### Secondary observation indexes

Ocular symptoms, diopter, and astigmatism are secondary indexes. Ocular symptoms will be evaluated before and after 30 days of training, respectively. Diopter will be obtained from the subjects after testing at the same hospital before and after the training.

#### Ocular symptoms

Ocular symptom scores are developed based on the “Visual Fatigue Test and Evaluation Method (VFTEM)” and principally cover eye fatigue, dryness, pain, visual double vision, neck pain, thought disorders, and lags in response.Collective Insufficient Symptoms Survey (CISS): the CISS is a valid tool in quantifying near visual acuity symptoms in adolescents [22] and consists of 15 items, each with five options of varying degrees, scored as follows: never (0), rarely (1), sometimes (2), often (3), and always (4). The sum of the 15 items’ scores (ranging from 0 to 60) is the total score.

All of the above information and scales need to be completed with the help of the subject student’s parents and professional staff.

#### Diopter and astigmatism

The diopter (after pupil dilation by tropicamide) and astigmatism will be obtained from the students after examination at a local first-tier public hospital or public eye hospital accompanied by their family members, and the data will be recorded in the entry of ‘Information Collection - Visual Acuity.”

Categorical variables, such as gender, age, etc., will be compared between groups. In particular, the effects of age on visual acuity will be stratified to reduce the variation.

## Data entry and statistical analysis

### Data collection

A paper version of the case report form will be developed for data collection. The data will be collected using standardized entry terms and structured registration contents as much as possible, which will facilitate post-processing and analysis of the data and minimize the burden on the researcher. According to the original observation records of the subjects, the data manager will load the data into the case report form in a timely, complete, correct, and clear manner. When amending a case, the original record should be clearly visible, and corrections should be signed and dated by the investigator.

### Data entry and storage

The paper-based data should be entered by a dedicated data manager using a dual-track entry to reduce the error rate, and any problems or unexpected matters found in the entry process should be registered and reported promptly so that problems can be dealt with quickly. Observation forms should be subject to random inspections at the end of data entry to understand the quality of the entry and to analyze and address any problems. Once data entry is completed, all original case report information should be kept. The original case report forms, after completion of data entry and verification as required, should be filed in a numbered order, and a dedicated person should be assigned to manage the files and complete the search directory, etc. Also, the entered data should be backed up regularly to prevent loss of data and other unexpected occurrences. Particular attention should be paid to the security of data storage and the protection of the privacy of the subjects and related personnel. All research documents will be stored in special filing cabinets that are locked to ensure the security of the stored documents. In any case, only authorized staff will have access to the data.

## Statistical analysis

### Sample size

The sample size will be estimated based on our early observations [23]. The treatment group was 4.98 ± 0.14, and the control group was 4.92 ± 0.24. Under 20% dropout rate, with the two-tailed *α* = 0.05 and *β* = 0.1 (test efficacy of 0.9), experimental group: control group = 2:1, PASS 15.0 software calculation shows 380 in the experimental group and 190 in the control group. Due to the possible center effect, the final sample size is suggested to be twice expanded. Thus, it is finally confirmed there will be 1140 cases in total, with 760 cases in the experimental group and 380 cases in the control group.

Statisticians suggest that we appropriately expand the sample size to reduce the impact of the central effect on the final results.

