### Study design

This study will be a prospective, multicenter, randomized controlled clinical trial. The included subjects (*n* = 1140) will be randomly assigned to the experimental (*n* = 760) and control (*n* = 380) groups in a 2:1 ratio. The aim of this study is to objectively evaluate the clinical efficacy of the guided meditation of vision training for adolescent myopia. This report will be compiled according to the SPIRIT (Standard Protocol Items: Recommendations for Interventional Trials) 2013 Statement “Defining Standard Protocol Items for Clinical Trials” (Fig. 1 and Table 1).

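### The base sample size of 380 + 190 gives about 81% power on the protocol's own inputs, not 90%, so part of the doubling for centre effect covers a shortfall in the base calculation

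*Protocol article*

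**What the plan says.** The Sample size section of the protocol article takes its inputs from earlier observations by the same group: "The treatment group was 4.98 ± 0.14, and the control group was 4.92 ± 0.24". The other settings are "with the two-tailed *α* = 0.05", a power given as "test efficacy of 0.9", allocation as "experimental group: control group = 2:1", and a dropout rate of 20%. From these, "PASS 15.0 software calculation shows 380 in the experimental group and 190 in the control group", which is 570 in total.

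The section then says: "Due to the possible center effect, the final sample size is suggested to be twice expanded". This produces the final 760 + 380 = 1140, which the Study design section repeats. No intraclass correlation or design effect is given. The section does not say how the two SDs were entered or how the dropout allowance was applied. The Recruitment, Randomization and Statistical analysis sections say that both arms run within the same school.

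**The concern.** The two SDs are clearly unequal, and the larger one (0.24) belongs to the control arm, which receives only a third of the children. The variance of the difference is therefore dominated by the smaller arm, and a correct calculation must carry that. A base size of 570 looked low for these inputs.

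If the base is too small, the protocol's 90% power claim is not met at the point where it is made. The factor of 2, which the protocol attributes wholly to centre effect, must then also cover the deficit, leaving less room for centres than the text implies. Phase 1 power matters here because the Second phase section makes continuation of the trial depend on the phase 1 comparison.

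**Working it through.** **Inputs** (all from the Sample size section): difference 4.98 − 4.92 = 0.06; SD 0.14 experimental and 0.24 control; two-sided alpha 0.05; power 0.90; 2:1; dropout 20%. (1.960 + 1.282)² = 10.507.

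**1. Can the stated 380 + 190 be reproduced?** Not by the standard calculation on these inputs (step 2). Three other routes come close:

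- Common SD 0.19, the plain average of 0.14 and 0.24. Control n = 10.507 × 0.19² × 1.5 / 0.06² = 158.05, experimental 316.1. Multiplying by 1.2 gives 189.7 and 379.3. With whole subjects at each step (159 and 318) it gives 191 and 382.
- A 1:1 Welch calculation with both stated SDs. This needs 227 per arm; 227/0.8 rounds up to 284, or 568 in total; splitting 568 at 2:1 gives 379 and 189.
- A one-sided normal calculation with both SDs, multiplied by 1.2: 192 and 385.

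Each departs from the stated specification. The first replaces the two SDs by their average and adds 20% instead of dividing by 0.8. The second is not a 2:1 calculation. The third is not two-sided and also adds 20% instead of dividing by 0.8.

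**2. Size needed on the stated inputs.**

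- Control n = 10.507 × (0.14²/2 + 0.24²) / 0.06² = 10.507 × 0.0674 / 0.0036 = 196.7; experimental 393.4. Rounded up: 394 + 197 evaluable.
- Dividing by 0.8: 491.8 and 245.9, so 492 + 246 = 738 enrolled.
- Welch t: 398 + 199 evaluable, 498 + 249 = 747 enrolled.

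The stated 570 is 168 below 738, or about 23% short.

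**3. Power of 380 + 190.**

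- After 20% loss (304 + 152): SE = √(0.14²/304 + 0.24²/152) = 0.02106; 0.06/0.02106 − 1.960 = 0.889; power 81.3% (Welch t 80.9%; simulated Welch test 81.1%).
- With no loss: SE = √(0.14²/380 + 0.24²/190) = 0.01883; power 89.0% (Welch t 88.8%).

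So even with no dropout the base figure falls slightly short of 90%.

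**4. Power of 1140 after 20% loss (608 + 304), by assumed design effect (Welch t).**

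| Design effect | Power |
|---|---|
| 1 | 98% |
| 1.25 | 95% |
| 1.5 | 91% |
| 1.75 | 86% |
| 2 | 81% |

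The largest design effect that still leaves 90% is 1140/738 = 1.54 (1140/747 = 1.53 on the Welch figure). Put the other way, the doubling splits into 738/570 = 1.29 that makes good the base shortfall and about 1.54 that remains for centres.

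**The case against.** The strongest reply is that the enrolled number is probably sufficient. The protocol attaches 90% to the base calculation, not to 1140. It speaks of a possible centre effect, and the doubling reads as a precaution, not a computed variance inflation. With both arms in every school, differences between schools largely cancel from the comparison. Separate classrooms and teachers for the two arms (Quality control section) may leave some clustering, but nothing in the document establishes a factor of 2. This stands. A reader might infer from the doubling that the trial has only 81% power; that needs a design effect of exactly 2, which the protocol never states. Nor is power above 90% at a small design effect a fault.

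A reader might also infer that the sponsor averaged the SDs and multiplied by 1.2. The document describes neither step, and the 1:1 total split 2:1 lands about as close while using the right SDs and the right dropout formula. The averaging route is one possible reconstruction and cannot be put as fact.

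Finally, because the more variable arm is the smaller one, a reader might conclude that allocation should change to 1:1. The 2:1 ratio is stated consistently and is a design choice. The Trial status section says recruitment is ongoing, with first enrolment in December 2021, before the January 2022 publication date, so it cannot be assumed that no child had been enrolled.

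None of this rescues the base figure. An equal-variance t-test does not either: at 304 + 152 it shows 88% power in simulation, but with a type I error of about 9.5%.

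**Conclusion.** The base size of 380 + 190 is wrong for the stated inputs, whichever route produced it. About 738 to 747 enrolled are needed, against 570, and 570 with 20% loss has about 81% power. Part of the doubling described as a centre-effect allowance therefore covers this deficit.

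The conclusion rests on the protocol's own means, SDs, alpha, ratio and dropout, with the two SDs kept separate and 20% dropout read as 80% evaluable in each arm. It does not show that 1140 is too few: on the same inputs 1140 meets 90% up to a design effect of about 1.54 and falls to 81% only at 2. Which applies cannot be settled from the document.

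**What to change.** Keep 1140 and correct the Sample size section. It should say that:

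- with SDs of 0.14 and 0.24 kept separate, 2:1 allocation, two-sided 0.05 and 90% power, the requirement is about 394 + 197 evaluable, or 738 enrolled after dividing by 0.8 (about 747 by the Welch t-test);
- 760 + 380 with 20% loss leaves 608 + 304, which gives about 98% power with no centre inflation, 90% up to a design effect of about 1.54, and 81% if the design effect is the full 2 implied by the doubling;
- the design effect assumed for this trial is a stated value, with the reason for it given the two arms within each school.

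The cost is wording only: enrolment, allocation and conduct do not change. The downside is that the stated power becomes less favourable, because the doubling can no longer be presented as a pure centre-effect margin on top of 90%.
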